##### Anxiety

This outcome is measured using the Spielberger State-Anxiety Inventory (STAI-State) [124], a 20-item self-report instrument developed to assess levels of relatively transient situation-related (state) anxiety. Items are rated on a 4-point Likert-type scale to produce a summative score ranging from 20 to 80 with higher scores indicating higher levels of anxiety. The STAI-State has been used widely in pregnancy and postpartum studies and anxiety has been consistently related to depressive symptomatology in new mothers [16].

##### Attachment

This outcome is measured using a revised version of Brennan, Clark, and Shaver’s Experiences in Close Relationships (ECR) questionnaire, the ECR-Revised (ECR-R) [125]. The ECR-R yields scores on two-dimensional subscales: attachment-related anxiety (that is fear of rejection and abandonment; items 1 to 18) and attachment-related avoidance (that is discomfort with closeness and discomfort with depending on others; items 19 to 36). Each item is rated on a 7-point scale that ranges from 1 (strongly disagree) to 7 (strongly agree). For the present trial, only those who report living with a spouse or partner in an intimate relationship complete this questionnaire.

##### Relationship quality and adjustment

This outcome is measured using the Dyadic Adjustment Scale (DAS) [126]. The DAS is a comprehensive, 32-item scale frequently used to measure adjustment in couple relationships, an aspect of relationship quality. Items are rated on Likert-type scales, with total DAS scores ranging from 0 to 150. A total DAS score may be derived by summing across the four subscales, each of which vary in length: dyadic consensus (items 1–3, 5, 7–15; score range 0 to 50), dyadic satisfaction (items 16–23, 31, 32; score range 0 to 24), dyadic cohesion (items 24–28; score range 0 to 65), and dyadic affectional expression (items 4, 6, 29, 30; score range 0 to 12) [126]. The DAS has demonstrated good psychometric properties with diverse populations and is commonly used in PPD studies [126,127]. Increased relationship quality and adjustment has been associated with decreased depressive symptomatology in postpartum women [127]. For this trial, only those who report living with a spouse or partner in an intimate relationship complete the DAS.

##### Health service utilization

This outcome is measured using a slightly modified version of the Health Service Utilization and Cost of Care Questionnaire [128], a self-report instrument developed and used by researchers at McMaster University’s Health and Social Service Utilization Research Unit. Previous research by [name] [129] suggests that mothers with depressive symptomatology in the early postpartum period used significantly more health services than mothers with no depressive symptomatology.

#### Other outcomes

##### Maternal evaluation of IPT

This outcome is measured using the Maternal Satisfaction with IPT Questionnaire. Based on (1) [name]’ previous maternal satisfaction questionnaires for the Breastfeeding [103] and PPD prevention trials [110,130], (2) the Client Satisfaction Questionnaire [131], and (3) the Patient Satisfaction Questionnaire [132], this outcome is assessed at 12 weeks post-randomization by the trial coordinator (who is not collecting any primary or secondary outcome data).

##### Nurse evaluation of IPT training and intervention

This outcome, assessed via telephone at the end of the trial, is measured using the Nurse IPT Experience Questionnaire. Based on similar content areas used in [name]’ previous trials [103], questions are related to (1) IPT training, (2) supervision, (3) provision of IPT, and (4) personal effects.

##### Nurse IPT activities

All intervention activities (for example, telephone discussions, left messages, missed sessions) are documented by the IPT nurses using the IPT Activity Log. IPT nurses are requested to return the activity log for a mother immediately post-treatment. This activity log is similar to ones used in [name]’ previous telephone-based trials [103,130], including the PPD prevention trial [110].

### Participants

#### Sample size

Two hundred and forty mothers >2 weeks and <24 weeks postpartum.

#### Justification for sample size

PPD psychosocial and psychological treatment trials have reported control group spontaneous recovery rates (EPDS < 13) ranging from 25 % to 40 % [130,133-136]. The difference in recovery rates between groups in these trials ranged from 27 % to 55 %, with 66 % to 85 % of mothers in the intervention group classified as non-depressed at the primary outcome time period. Among perinatal IPT trials (including both antenatal depression and PPD) where participant inclusion criteria included a clinical diagnosis of depression, reported control group spontaneous recovery rates (for example, HRDS < 7, BDI < 10) ranged from 15 % to 18.3 % [75,77]. The difference in recovery rates between groups in these trials ranged from 16.7 % to 44.6 %, with 32 % to 60 % of mothers in the intervention group classified as non-depressed at the primary outcome time period. These results should be interpreted with caution, due to the different methods of measuring depressive symptomatology and small sample sizes. In the most rigorous IPT trial for PPD (*n* = 120), 38.3 % of mothers in the IPT group and 18.3 % of mothers in the control group were classified as non-depressed immediately post-treatment (that is 12 weeks post-randomization), a 20 % difference [77].

Given that (1) all the preceding studies used self-report measure to assess recovery (for example, no depressive symptomatology using a specific cutoff score) instead of a diagnostic interview such as the SCID, and (2) the proposed trial’s sample will be heterogeneous and include rural and urban mothers from diverse provinces, for the purpose of calculating the sample size, we have made the conservative assumption that 30 % of mothers in the control group will spontaneously recover and will not have major depression at the 12 week post-randomization assessment (70 % will remain clinically depressed) (Table 2). The sample size is based on the ability to detect a moderate decrease of 20 percentage points to a rate of 50 % among mothers in the intervention group. Our partners in the participating public health departments agree that a 20 % absolute decrease in the number of mothers with depression post-treatment is the minimum effect that would be considered clinically meaningful, warranting the time and effort to develop and implement an IPT program. A two-tailed α error of 0.05 was chosen, as there is insufficient empirical evidence of either risk or benefit associated with the proposed telephone-based IPT intervention. Thus, with 80 % power, a two-tailed α error of 0.05, and using a test of two independent proportions to find a 20 % reduction in the number of mothers with depression at 12 weeks post-randomization (immediately post-treatment for mothers in the intervention group), a sample size of 188 (94 per group) is required; we plan to enroll 240 to allow for up to 20 % loss to follow-up. This sample size also provides power to detect a 20 % absolute reduction in other secondary outcomes, such as anxiety.

**Table 2 T2:** Sample size differences between groups

**Control group depression rate**	**IPT group depression rate**	**Size per group**
75	55	88
70	50	94
5	45	96

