### Statistical analysis plan

#### Primary analysis

Data will be analyzed using SAS software and an intent-to-treat approach will be used. Every effort will be made to collect follow-up data from all participants. We will not impute a score for missing primary outcome data. A two-sided significance level of 0.05 will be used for the primary outcome; a significance level of 0.01 (two-sided) will be used for secondary and other outcomes to account for multiple comparisons. The demographic and other baseline variables will be compared between study groups using descriptive statistics (means, standard deviations, proportions). For the primary analysis, a two sample two-sided test of proportions will be used to compare the difference in the incidence of PPD (major depression using the SCID) at 12 weeks post-randomization between the intervention and control groups. For secondary analyses, the statistical method to compare groups will depend on the distribution of the outcome variable in question. For binary variables (for example EPDS score > 12), a contingency table chi-square for a 2 × 2 table will be calculated and presented together with estimates for the relative risk, relative risk reduction, absolute risk reduction, and the number needed to treat. The corresponding 95 % confidence intervals for each estimated parameter will also be provided. Covariate variable adjustment will be achieved using logistic regression. For ordered categorical variables, a chi-square for trend will be calculated. Relative risks for each category versus a base category will be presented. Continuous variables with repeated measurement (such as anxiety) will be first analyzed using a single, repeated measures MANOVA consisting of group and time factors to test for the study’s overall intervention, time, or interaction effect. Following the detection of a significant effect, separate repeated measures 2-factor analyses of variance (RANOVA) with appropriate contrasts will show the nature of the effect within each outcome variable. Covariate variable adjustment will be achieved using analysis of covariance and linear regression. Finally, the relationship between the number of IPT sessions on PPD, and other study outcomes will be assessed to determine an effective dose response.

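### The power claim for secondary outcomes carries over a sample size computed at 0.05, but those outcomes are tested at 0.01, where a 20-point difference has about 59% power at the article's 70% vs 50% rates

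*Protocol article*

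**What the plan says.** All references are to the Protocol article.

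- **Justification for sample size.** The trial is sized "with 80 % power, a two-tailed α error of 0.05, and using a test of two independent proportions". In the control group "70 % will remain clinically depressed" is assumed, and the aim is to "detect a moderate decrease of 20 percentage points to a rate of 50 % among mothers in the intervention group". This gives 94 per group (188 in total). Enrolment of 240 allows for up to 20% loss. The closing sentence adds that this sample also gives power for a 20% "absolute reduction in other secondary outcomes, such as anxiety". That sentence states no power level, significance level, base rate or standard deviation of its own.
- **Statistical analysis plan, Primary analysis.** The main comparison keeps the threshold used for sizing, two-sided 0.05. Everything else faces a stricter one: "a significance level of 0.01 (two-sided) will be used for secondary and other outcomes to account for multiple comparisons". Binary secondary outcomes, such as EPDS above 12, are compared by a 2 × 2 chi-square test. For the relative risk, absolute risk reduction and related estimates, 95% "confidence intervals for each estimated parameter will also be provided". Anxiety is given as an example of a continuous repeated measure, analysed by repeated measures MANOVA.
- **Secondary outcomes, Anxiety.** STAI-State items are summed "to produce a summative score ranging from 20 to 80". No cut-off is defined.

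**The concern.** The power sentence directly follows a calculation at 0.05 and uses the same 20-point effect. A reader will take it to mean roughly the same 80% power. The analysis section then sets a stricter threshold for exactly these outcomes, and the same number of mothers cannot give the same power at 0.01 as at 0.05 for the same rates.

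The secondary questions include SCID depression at 24 and 36 weeks and EPDS at every visit. For depression, the article calls a 20-point absolute decrease the minimum that is clinically meaningful. If a true effect of that size is missed about four times in ten, a non-significant secondary result says much less than the power sentence suggests.

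The one outcome that the sentence names has a separate problem: an absolute percentage reduction is a statement about proportions, and anxiety is not analysed as one.

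**Working it through.** **Inputs.** Control 70%, intervention 50%, two-sided 0.05, 80% power, 94 per group, 240 enrolled with up to 20% loss (Justification for sample size); two-sided 0.01 for secondary outcomes (Primary analysis). Evaluable numbers: 94 per group as stated; 240 × 0.8 / 2 = 96 per group after the planned loss; 120 per group with no loss.

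**Step 1: reproduce the stated size.** The formula is the two-proportion one with pooled variance under the null and no continuity correction:

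n = [z(1−α/2)·√(2p̄(1−p̄)) + z(power)·√(p₁(1−p₁) + p₂(1−p₂))]² / (p₁−p₂)²

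With p₁ = 0.70, p₂ = 0.50, p̄ = 0.60:

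n = [1.960 × 0.6928 + 0.8416 × 0.6782]² / 0.04 = 93.0 per group.

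The article states 94, so its figure reproduces. 188 / 0.8 = 235, which 240 covers. Power at 0.05 with 94 per group is 80.4%.

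**Step 2: same sample at 0.01.**

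power = Φ{[(p₁−p₂) − z(1−α/2)·√(2p̄(1−p̄)/n)] / √[(p₁(1−p₁) + p₂(1−p₂))/n]}

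With n = 94 and z = 2.576:

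power = Φ[(0.200 − 0.1841) / 0.06995] = Φ(0.228) = 59.0%.

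Exact enumeration of the chi-square test gives 58.9%, the unpooled formula 61.1%, and a continuity correction 53.0%. The result does not hinge on the formula.

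**Step 3: vary the evaluable number (70% vs 50%, 0.01).**

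| Per group | Basis | Power |
|---|---|---|
| 94 | stated requirement | 59.0% |
| 96 | 240 less 20% | 60.2% |
| 108 | 120 × 0.90, the response goal under Loss to follow-up | 67% |
| 120 | no losses | 72.5% |

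80% power needs 138.7, so 139 per group. That is 278 evaluable, or 278 / 0.8 = 348 enrolled.

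**Step 4: vary the control rate (20-point drop, 94 per group, 0.01).** Justification for sample size reports control recovery, defined as EPDS below 13, of 25–40%. So 60–75% of controls would still score above 12, which is this trial's binary EPDS outcome.

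| Control rate | Power |
|---|---|
| 30% or 90% | 81.1% |
| 40% or 80% | 66.5% |
| 50% or 70% | 59.0% |
| 60% | 56.7% |
| 75% | 62.0% |

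Over the EPDS range of 60–75%, power is therefore 57–62%. The Background section puts the share still clinically depressed at 6 months postpartum at 50%; a drop from 50% to 30% again gives 59%.

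**Step 5: detectable difference.** With 94 per group at 0.01, starting from 70%, power reaches 80% at a difference of about 24 points (24.4).

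**Step 6: anxiety.** The article gives no standard deviation or cut-off, so a 20% absolute reduction cannot be converted into an effect size. As an illustration only, take a single comparison of two means with 94 per group. A standardised difference of 0.41 has about 80% power at 0.05 and about 59% at 0.01; 80% power at 0.01 needs about 0.50. This ignores the repeated measures, whose correlation is not given.

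**Step 7: intervals.** At 70% vs 50% with 94 per group, the chance that p falls between 0.01 and 0.05 is 80.4% − 59.0% = about 21%. In those cases the 0.01 test is not significant, while the 95% interval will generally exclude no effect.

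**The case against.** The strongest reply is that the article never attaches 80% to secondary outcomes. It says only that the sample gives power, with no level, so no printed number fails to reproduce. That is literally correct: 80% is an inference from context. But if some other level was meant, the sentence tells the reader nothing, and the mismatch between 0.05 and 0.01 remains.

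A second reply is that 59% is itself conditional. This stands. It uses the primary outcome's rates and the minimum evaluable number, and power rises to 81% at control rates of 30% or 90%. The article assumes neither rate for any outcome, however. For control rates of 40–80%, power stays below 80% even with all 120 per group.

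A reader might infer several stronger things that the documents do not support:

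- **That 59% describes anxiety.** It does not, because anxiety is not a proportion here.
- **That power is as low as 46%.** That needs 74 per group, which is 120 × 62%, the average retention of longer follow-up studies that Loss to follow-up cites as a threat. The article plans for at most 20% loss, aims for a 90% response rate, and cites 85% retention at 24 weeks in an earlier trial.
- **That the 95% intervals contradict the 0.01 rule.** The decision rule is the test. Intervals may be given at another level for estimation, and the article nowhere says that significance is read from them. This is a mismatch.
- **That the trial is too small for its primary question.** Step 1 shows that the primary calculation holds.

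**Conclusion.** The point holds for binary secondary outcomes. The power that the sentence implies is not available at the significance level the article sets for them: about 59–60% at 70% vs 50% with 94–96 per group, 57–62% for control rates of 60–75% with 94 per group, and 72.5% at 70% vs 50% with no losses. These figures assume equal groups, a 20-point difference and the stated control rates. For anxiety the claim cannot be checked, because the effect it names is undefined for a continuous score.

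The interval level is a side issue of presentation. The primary outcome, its test and the enrolment target are untouched. The severity is moderate to minor: a stated design property needs correcting, but no planned test changes.

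**What to change.** Restate or withdraw the closing power sentence under Justification for sample size.

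- **If restated:** give power at two-sided 0.01 with the assumed rates and evaluable number. An example is about 59–60% power for 70% vs 50% with 94–96 per group, or about 24 points below 70% detectable with 80% power at 94 per group. The conditions should be printed beside the figure, so that 59% is not read as applying to every secondary outcome.
- **Anxiety:** give any power as a standardised mean difference, with its assumed standard deviation and, if the repeated measures are used, the assumed correlation. Otherwise drop it as the example.
- **Optional:** report 99% intervals alongside the 95% ones for outcomes tested at 0.01, or add a sentence that significance is judged by the 0.01 test alone.

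The cost is a text correction and, if the option is taken, one extra interval level in the programs. The stated power becomes less favourable. Sample size and the primary analysis do not change.

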#### Inclusion criteria

Inclusion criteria are: (1) live birth; (2) mother 2 to 24 weeks postpartum; (3) infant discharged from hospital and at home with mother; (4) clinical diagnosis of major depression using the SCID-I; and (5) understands spoken English. Due to the nature of the intervention, it is not feasible to recruit mothers unable to speak English.

#### Exclusion criteria

Exclusion criteria are: (1) current use of antidepressant or antipsychotic medication; (2) currently receiving any form of individual psychotherapy administered by a trained professional; (3) active suicidal or self-harm thoughts; (4) current or past manic depression or bipolar diagnosis; and (5) chronic depression (episode length > 2.0 years). These exclusion criteria are consistent with other IPT trials [71,72,77].

### Trial process

#### Referrals

Referrals for the trial come from a variety of sources including public health departments, mental health units, and private practice clinics.

#### Public health

Currently, 24 public health departments across Canada (Ontario, Manitoba, Saskatchewan, and British Columbia) are assisting with recruitment for this trial. In Canada, public health departments receive notification of women who have given birth in their health region. As part of standard practice, each mother receives a telephone call or home visit from a public health nurse within the first few weeks postpartum following hospital discharge. During these interactions, public health nurses often administer the EPDS to assess maternal mood. A brief description is provided to mothers who are identified as experiencing depressive symptomatology (EPDS > 12) after the first 2 weeks postpartum (in order to avoid false-positives that are ‘maternity blues’). If verbal consent is obtained, the potentially eligible mother’s contact information is sent to the trial coordinator.

#### Other health professionals

In addition to referrals from public health departments, health professionals in public or private practice across Canada may also refer potentially eligible mothers.

#### Self-referrals

Women who are between 2 and 24 weeks postpartum and self-identify as feeling down or depressed may also self-refer to the trial.

All referred mothers are contacted by the trial coordinator and provided a detailed explanation of the study. If the mother expresses interest in participating in the trial, she is further assessed for eligibility. Eligible women are asked to provide verbal consent to participate in the study; if she consents, baseline information is collected by the trial coordinator. Using a web-based, centrally controlled randomization service, the mother is randomized to either the control (standard postpartum care) or intervention group (standard postpartum care plus 12 telephone-IPT sessions), with stratification based on province and self-reported history of depression. Following randomization, participants are immediately informed of their study group assignment.

#### Consent

Two copies of the study explanation and participant consent form are mailed to each participant. A postage-paid, addressed envelope is included in the mailed package so that one copy of the signed consent form is returned to the trial coordinator and the other copy is retained by the participant for her own records. These informed consent procedures have been used effectively by [name] in previous trials [110,130].

With detailed informed consent procedures, it is expected that mothers will accept their group allocation following randomization. While most health professionals caring for participants and research nurses will be blinded, mothers cannot be. However, a formal telephone-based IPT PPD program does not already exist in the participating health regions, thereby ensuring no mother in the control group will receive the intervention. There will be no interference with usual medical/nursing care, which for some mothers may include antidepressant medication and/or psychotherapy. Very few mothers will have available and receive psychotherapy. As such, the actual number of trial participants in the control group who will receive psychotherapy will be very small; data about the presence of psychotherapy external to the trial will be collected during the health service utilization assessment. Information about interventions to treat PPD will be obtained from the participants and considered in the data analyses.

#### Treatment

Mothers allocated to the treatment group are contacted by the IPT nurse within 72 h of trial randomization and then weekly thereafter for 12 sessions.

#### Post-randomization data

To assess compliance to IPT, all intervention activities (for example telephone discussions, left messages, missed sessions) are documented by the IPT nurses using the IPT Activity Log. IPT nurses are requested to return the activity log for a mother immediately post-treatment.

#### Follow-up

Research nurses blinded to participant group allocation telephone study participants at 12, 24, and 36 weeks post-randomization/post-treatment to determine trial outcomes. PPD at 12 week post-randomization was chosen as the primary outcome because (1) we desire to provide comparable results to other perinatal IPT trials [73-80], and (2) the likelihood of losses to follow-up increase over time. So as to (1) address criticisms of previous trials related to insufficient follow-up to determine the longer-term effects of IPT and (2) present comparable results to other PPD treatment trials [137,138] including IPT trials [77,78], participants are contacted again at 24 and 36 weeks post-randomization and assessed for PPD and other outcomes (Figure 1).

